### 2.6. Randomization and Allocation Concealment

Participants will be randomly assigned to the YGJ, PWS, and usual care groups at a 2:2:1 ratio at the baseline visit (Visit 2). This allocation ratio was set in consideration of previous research [11,19] and ethical aspects. A random number will be generated using SAS^®^ Version 9.4 software (SAS Institute Inc., Cary, NC, USA) by a statistician ([name]) independent of the trial procedure and assessment. The block randomization method will be used in block sizes of 5 and 10 with no stratification. For allocation concealment, the randomization code will be sealed in opaque envelopes and stored in locked cabinets in each trial institution. If the participants who voluntarily signed the written informed consent are able to participate in this clinical trial by meeting the eligibility criteria, the investigator opens the randomization envelope in front of the participants in order and assigns them to one of three groups. The date of opening and the signature of the investigator will be written on the opened envelope, which will be stored separately.

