### 2.4. Exclusion Criteria

Diagnosed with specific diseases, including peptic ulcer, esophageal cancer, MALT lymph cancer, stomach cancer, colon cancer, biliary tract and pancreatic diseases (except asymptomatic cholelithiasis), and inflammatory bowel disease within 1 year prior to the screening visit;Having more severe symptoms of reflux esophagitis and irritable bowel syndrome than those of dyspepsia (Participants with reflux esophagitis or irritable bowel syndrome can participate in this clinical trial. However, through the participants’ interview and medical history taking, participants whose symptoms of reflux esophagitis (including reflux and heartburn) and irritable bowel syndrome (including abdominal pain or discomfort related to the pattern of defecation) are more severe than those of dyspepsia are excluded.);Having alarming symptoms such as severe weight loss, bloody stool, dysphagia, swallowing pain, and persistent vomiting;Diagnosed with mental disorders, such as major depressive disorder, anxiety disorder, and panic disorder, or having a depression score of 11 or higher on the Hospital Anxiety and Depression Scale (HADS) at the screening visit;Having serious systemic diseases in heart, lung, liver, or kidney, or presence of other malignant diseases;Having a history of gastrointestinal surgery (except for appendectomy more than 6 months ago);Taking medications that can affect the gastrointestinal tract, including proton pump inhibitors, histamine receptor antagonists, antacids, prokinetics, antidepressants, gastric fundus relaxants, gastric mucosal protectants, nonsteroidal anti-inflammatory drugs, anticholinergics, or oral corticosteroids, or receiving *Helicobacter pylori* eradication treatment, within 2 weeks prior to the screening visit (taking low-dose aspirin (100 mg/day or less) for the purpose of preventing cardiovascular disease is allowed);Having received Korean medicine treatments such as acupuncture, herbal medicine, or moxibustion for the purpose of improving dyspeptic symptoms within 2 weeks prior to the screening visit, or who are planning to receive them during the trial period;Having severe liver or renal diseases (aspartate aminotransferase or alanine aminotransferase levels ≥ 3 times the upper limit of normal levels or creatinine levels ≥ 2 times the upper limit of normal levels);Having a history of alcohol or drug abuse;Women who are pregnant or lactating, or women who do not agree to use effective methods of contraception during the clinical trial;Having genetic problems, such as galactose intolerance, Lapp lactase deficiency, or glucose-galactose malabsorption;Having known hypersensitivity to investigational products (according to the Korean Ministry of Food and Drug Safety (KMFDS), adverse events such as pseudoaldosteronism, myopathy, and skin reactions (rash, redness, itching, hives) may occur after the administration of YGJ and PWS.);Having taken other investigational products within 3 months; andHaving judged to be unsuitable for participation in this trial by investigators.

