### 2.7. Blinding

Because it is not possible to blind the participants due to the nature of group assignment, we designed the trial to blind the outcome assessor to minimize the related bias. The effect evaluation of the participants will be conducted by an investigator who will not prescribe the investigational product and will not have access to any source documents, including medical records and case report form (CRF). The outcome assessor only asks questions related to the evaluation items and does not know which group the clinical trial participants are assigned to.

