### 2.10. Sample Size Calculation

The primary objective of this study is to compare and evaluate the effectiveness of 6 weeks of administration of YGJ compared to usual care in participants with FD. We will test whether there is a difference in the degree of reduction in TDS scores between the two groups after 6 weeks through a superiority test. Based on the results of a previous study comparing YGJ and a placebo [19], and considering the 15% placebo effect, it is assumed that the difference between the average TDS change between the YGJ and usual care groups after 6 weeks is 2.70, and the standard deviation is 3.65. The significance level is 0.05, and the power is 80%. Taking into account the previous studies [11,19] and ethical issues, the ratio between the YGJ and usual care groups is assigned at 2:1. Therefore, 44 and 22 participants are required for the YGJ and usual care groups, respectively.

Additionally, the second purpose of this study is to evaluate the noninferiority of YGJ compared with that of PWS. For this, the noninferiority margin should be defined based on the results of the effect evaluation between the PWS and usual care groups. However, due to the lack of prior research and related data, we will first test the superiority of PWS compared to usual care after 6 weeks to define the noninferiority margin. Under the assumption that the effect size of the YGJ and PWS is the same, 44 participants are also required in the PWS group. Therefore, considering the 20% dropout rate, a total of 140 participants, including 56, 56, and 28 participants in the YGJ, PWS, and usual care groups, respectively, are required.

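### With open treatment, site-held envelopes opened in order and stated blocks of 5 and 10, enrolling staff can infer the next assignment better than chance; one central shared list would largely close this route

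*Protocol article*

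**What the plan says.** All references are to the protocol article.

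- **Section 2.6** sets a 2:2:1 allocation (YGJ, PWS, usual care) at Visit 2, from a list made by a statistician "independent of the trial procedure and assessment". On blocking: "The block randomization method will be used in block sizes of 5 and 10 with no stratification". On storage: "the randomization code will be sealed in opaque envelopes and stored in locked cabinets in each trial institution". On use: "the investigator opens the randomization envelope in front of the participants in order and assigns them to one of three groups". This follows consent and confirmed eligibility, and the opened envelope is dated, signed and kept.
- **Section 2.7** leaves treatment open: "Because it is not possible to blind the participants due to the nature of group assignment". Only the outcome assessor is blinded.
- **Section 2.4** ends with a discretionary exclusion for anyone "judged to be unsuitable for participation in this trial by investigators".
- **Table 1** puts eligibility screening and consent two weeks before allocation.
- **Sections 2.10 and 2.11** give 28 usual care participants (22 before the dropout allowance). They serve Hypotheses 1 and 2. Hypothesis 3 is tested only if both succeed, and its noninferiority margin is a confidence limit from Hypothesis 2.

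The article does not say how one unstratified list is divided among the three hospitals, or that block sizes are kept from enrolling staff.

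**The concern.** Opaque envelopes and locked cabinets stop staff from looking ahead. They do not stop deduction. Every opened envelope shows an assignment, and in a small block of known size the past assignments change the odds of the next one. Assessor blinding acts only after allocation.

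Usual care is the arm without an investigational product, so it is the slot that staff or patients are most likely to want to avoid or target. If usual care looks likely or impossible next, a participant could be excluded late, or Visit 2 could be brought forward or put back. The arms would then differ in who entered them. The endpoint is a subjective symptom score, so such a difference can carry into the result. The usual care arm is the smallest, and all three hypotheses depend on it: two directly, and the third through the gate and the margin.

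**Working it through.** **1. The plan's own figure.** Inputs from section 2.10: "it is assumed that the difference between the average TDS change between the YGJ and usual care groups after 6 weeks is 2.70", SD 3.65, two-sided 5%, power 80%, ratio 2:1.

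n(usual care) = (1 + 1/2) × (1.960 + 0.842)² × 3.65² / 2.70² = 1.5 × 7.85 × 1.8275 = 21.5, so 22, with 44 for YGJ. With 20% dropout, 22/0.8 = 27.5, so 28, and keeping 2:2:1 gives 56/56/28 = 140. The stated size reproduces. The present point does not change it.

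**2. How deduction works.** In a block of size s with T slots for an arm, after m assignments of which k went to that arm, P(next is that arm) = (T − k)/(s − m). This is averaged over block sizes that fit the history. Take sizes 5 and 10 as equally likely, at the start of a list:

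- First envelope is usual care. This has probability 1/5 under size 5 and 2/10 under size 10, so the sizes stay equally likely. P(next is usual care) = ½ × 0 + ½ × 1/9 = 5.6%, against a nominal 20%.
- First four are YGJ, YGJ, PWS, PWS. This has probability 1/30 under size 5 and 1/35 under size 10, so P(size 5) = 35/65 = 0.538. P(next is usual care) = 0.538 × 1 + 0.462 × 2/6 = 69%.

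**3. Hand checks when block boundaries are known.**

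- Blocks of 5: the usual care slot is equally likely at each place, so on average 2 of 5 places follow it. Usual care is ruled out for 40%. The next arm is certain for (1 + 0.2)/5 = 24%, where 0.2 is the chance that the last two places match.
- Blocks of 10: the second usual care slot falls on average at 2 × 11/3 = 7.33, so usual care is ruled out for 2.67/10 = 27%. The next arm is certain for (1 + 0.289 + 0.067 + 0.010)/10 = 14%.

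**4. Simulation of the plan.** Assumptions: a contiguous run of 140/3 ≈ 47 envelopes per site, and a guesser who knows both sizes and all past assignments at the site.

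| Block pattern | Best guess right | Next arm certain | Usual care ruled out |
|---|---|---|---|
| No information from the past | 40% | 0% | 0% |
| 5 and 10, order unknown | 57% | 6% | 13% |
| 5 and 10, order known | 57% | 16% | 30% |
| All blocks of 5 | 61% | 24% | 40% |
| All blocks of 10 | 56% | 14% | 27% |

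In the second row, the predicted chance of usual care just before allocation averages 0.36 for those who get it and 0.16 for those who get YGJ. It exceeds 20% for 74% of the former and 33% of the latter, a difference of 0.41.

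**5. Alternatives.**

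- Wider blocks at each site (5, 10, 15, 20 in random order): best guess 53%, certain 1.3%, usual care ruled out for 3%. The 0.41 difference falls only to 0.33.
- One list of 5s and 10s shared by three equal sites, interleaved at random, with a guesser who sees only the own site but knows the sizes and each position on the list: best guess about 45%, certain 0%, usual care ruled out for about 0.6%.
- The same shared list with the block order also known: the formula in step 2, counting only the site's own assignments in m and k, gives about 45%, 0.3% and 6%. Withholding the block structure therefore matters as well.

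**The case against.** A fair opponent would make five points.

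- **Prediction is limited.** Even a perfect tracker is wrong 43% of the time and certain for only 6%. Mixing two sizes is itself a protection. This stands. A reader might infer that the next assignment can often be predicted, or that every five envelopes hold exactly one usual care slot. The first overstates the rates. The second is true only of blocks of 5, because a block of 10 can hold its two slots anywhere.
- **The premises are partly inferred.** The text says only that the investigator opens the envelope; that the same person judges eligibility is a fair reading, not a statement. Whether site papers show the block sizes cannot be seen from an article. If one list is interleaved across sites, prediction is weaker than in the plan's row of the table. These qualifications stand. Envelopes stored at each hospital and opened in order do make a contiguous run the natural reading.
- **The steering route is narrow.** Screening is two weeks before allocation. June 2022 to December 2023 less about 26 weeks leaves roughly 13 months, or 140/3/13 ≈ 3.6 entries per site per month if recruitment is even. Typically fewer than two people per site would be in run-in together. This lowers the likely harm, but late exclusion and the timing of Visit 2 remain.
- **There are safeguards.** Envelopes are opened in front of the participant, dated, signed and stored, and monitors visit regularly (section 2.13). These deter out-of-order opening but do not prevent deduction.
- **Analysis can help.** Section 2.11 allows adjustment for imbalanced variables or those that can affect dyspepsia. This could remove steering on measured severity, but not on something unmeasured such as treatment-seeking. It would be wrong to say that analysis can remove none of it.

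**Conclusion.** The weakness is real but moderate. As written, section 2.6 combined with section 2.7 lets staff who enrol infer the next assignment better than chance: about 57% right against 40%, certain for about 6%, usual care ruled out for about 13%. These rates assume contiguous runs of about 47 envelopes per site, sizes 5 and 10 equally likely in random order, and a guesser who tracks everything. They are upper values for staff who track less, and would be higher only if the block order were known.

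A reader might go further and infer a definite bias or an inflated error rate. With SE = 3.65 × √(1/44 + 1/22) = 0.953, a bias of 0.35 to 0.5 TDS points would raise the two-sided 5% error to about 6.5% to 8.1%. But the bias would be about 0.41 × d, where d is the average shift in expected TDS change among participants entered when usual care looks likelier than 20%. Nothing in the document fixes d, or shows that steering would occur. The supportable conclusion is an avoidable opening for selection bias in Hypotheses 1 and 2, and through them in Hypothesis 3, of unknown size.

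**What to change.** For participants not yet randomised:

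1. Replace the site-held envelopes with one central unstratified list shared by the three hospitals. The independent statistician or the existing data management team can hold it. A central list that is still blocked by site would be as guessable as the envelopes.
2. Release each assignment singly, only after the participant is irrevocably registered as eligible at Visit 2.
3. Withhold block sizes and block order from enrolling staff. Larger sizes in random order are an optional addition; used alone at each site they help little.
4. State how the list is, or was, divided among the sites.

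The cost is a regenerated list, an amendment with IRB approval, and a short web or phone step at Visit 2. The data management team and web-based CRF already exist. Balance at 2:2:1 within a site will be slightly less exact. No extra participants or procedures are needed.

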**Hypothesis** **1.**
*[*

$H_{0}\;:\;\mu_{1}=\mu_{2},\;H_{1}\;:\;\mu_{1}\neq \mu_{2}$

*]*

*-*

$\mu_{1}$

*: Change in TDS score of the YGJ group at week 6*

*-*

$\mu_{2}$

*: Change in TDS score of the usual care group at week 6*

A two-sided test with a significance level of 5% will be conducted using a mixed-effect model repeated measure (MMRM) with participants as the random factor and the treatment group and time of visit as the fixed factors. If necessary, analyses will be performed by setting variables showing statistically significant differences in demographic characteristics or variables that can affect dyspepsia as the fixed factors. The second purpose of this study is to evaluate the noninferiority of YGJ compared to that of PWS (Hypothesis 3). Consequently, the noninferiority margin (*M*) will first be defined based on the results of the effect evaluation of PWS compared to usual care at week 6 (Hypothesis 2), and the analysis method will be the same as that of Hypothesis 1.

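### The protocol does not say how an unstratified block list is divided among three hospitals that each hold envelopes, and the primary model has no pre-specified term for institution

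*Protocol article*

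**What the plan says.** Section 2.1 names three recruiting hospitals. Section 2.6 fixes a 2:2:1 allocation and the method: "The block randomization method will be used in block sizes of 5 and 10 with no stratification". On concealment it adds that "the randomization code will be sealed in opaque envelopes and stored in locked cabinets in each trial institution", and that the investigator opens the envelopes in order with the participant present. How a list without strata is shared among three cabinets is not stated.

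The primary analysis, under Hypothesis 1 in section 2.11, is a repeated-measures mixed model "with participants as the random factor and the treatment group and time of visit as the fixed factors". Institution is not named. A further sentence allows extra fixed factors if necessary: variables that differ significantly among the demographic characteristics, or variables that can affect dyspepsia. Section 2.11 applies the same method to Hypotheses 2 and 3 and to the secondary outcomes.

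**The concern.** With three sets of envelopes, the list must have been divided in some way, and the division decides what the blocks achieve. Whole blocks or consecutive runs give near-balance within each hospital, which is blocking by site under a no-stratification label. Blocks split across hospitals give no balance within a hospital. The analysis should reflect whichever applies, and the stated model is silent on institution in both cases.

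The usual care arm makes this worth settling. It has 28 randomised and 22 evaluable participants and is the comparator for Hypotheses 1 and 2. The lower confidence limit from Hypothesis 2 becomes the noninferiority margin for Hypothesis 3. Lost precision on this arm therefore carries through the whole fixed sequence. Participants are not blinded and the endpoint is a symptom score, so differences between hospitals in mean change are plausible, although the protocol gives no data on them.

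**Working it through.** **Inputs from the protocol.** Section 2.10: "it is assumed that the difference between the average TDS change between the YGJ and usual care groups after 6 weeks is 2.70"; "the standard deviation is 3.65"; "the ratio between the YGJ and usual care groups is assigned at 2:1"; "The significance level is 0.05, and the power is 80"% (two-sided, from section 2.11: "A two-sided test with a significance level of 5% will be conducted"); 20% dropout; 56/56/28 randomised.

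**Assumptions, not in the protocol.** Site sizes of 47/47/46, or 80/40/20 as an unequal case; site share of the variance of change 0 to 10%; one site's mean change differing by 1 TDS point.

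**1. The plan's own figure.**
- Usual care n = 1.5 × [3.65 × (1.960 + 0.842) / 2.70]² = 21.5, so 22, with 44 for YGJ. This reproduces the plan.
- Dropout: 22 / 0.8 = 27.5, so 28. Doubling gives 56, 56 and 28, total 140.
- Standard error at 44/22 = 3.65 × √(1/44 + 1/22) = 0.953.
- Power = Φ(2.70/0.953 − 1.96) = Φ(0.873) = 0.81.

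**2. Usual care patients per site.** Simulation of 8,000 runs, random blocks of 5 and 10 at 2:2:1, N = 140; the ranges are 95% ranges.

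| How the list is divided | 47/47/46 | 80/40/20 | A site off by 3 or more |
|---|---|---|---|
| Separate blocked list per site | 8–10 | 15–17, 7–9, 3–5 | no run |
| One list cut into consecutive runs | 8–11 | 15–17, 7–9, 3–5 | no run |
| One list scattered over sites | 5–14 | 11–20, 4–12, 1–7 | 37% (equal), 43% (unequal) |

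**3. Effect of imbalance on the estimate.** The shift in the YGJ versus usual care contrast is the difference between the arms in the share of patients at the deviating site, times 1 point. With near-equal sites its 95% limit is 0.04 (separate lists), 0.05 (consecutive runs) and 0.21 (scattered). Against a standard error of 0.953, the largest is 0.21/0.953 = 22% of one standard error. The shift is equally likely in either direction.

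**4. Effect of omitting site when allocation is in effect blocked by site.** With a site share s, the standard error with site modelled is 0.953 × √(1 − s):
- s = 5%: 0.929, so the unadjusted one is too large by a factor of 0.953/0.929 = 1.03.
- s = 10%: 0.904, a factor of 1.05.
- Power with site modelled: Φ(2.70/0.929 − 1.96) = 0.83 and Φ(2.70/0.904 − 1.96) = 0.85, against the planned 0.81.
- The estimate itself is already more precise under such blocking, so power without the site term is Φ[(2.70 − 1.96 × 0.953)/0.929] = 0.815 and, with 0.904, 0.821. The gain from the model term alone is thus about 1 to 3 points.
- Margin, if PWS also achieves 2.70: lower limit 2.70 − 1.96 × 0.953 = 0.83, against 0.88 (s = 5%) or 0.93 (s = 10%) with site modelled.

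**5. Effect of adding site when allocation was scattered.** Residual imbalance inflates the variance of the contrast by about 3% on average (simulated factor 1.033 at 44/22). Power becomes Φ[2.70/(0.953 × √((1 − s) × 1.033)) − 1.96] = 0.80, 0.82 and 0.84 for s = 0, 5% and 10%. Break-even is at s = 1 − 1/1.033, about 3%.

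**The case against.** The case against is substantial.

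- **In order does not have to mean one order across hospitals.** A site with a consecutive run of numbered envelopes can follow it, and no stratification may mean only that no factor was used to generate the list. This stands: a reader might infer that the procedure is unworkable or self-contradictory, and the text does not support that. What remains is that the division is unstated, and it determines what the blocks do.
- **Marked imbalance is not implied.** A reader might infer that the 28 usual care patients will be spread unevenly over sites. That follows only if the list is scattered without regard to blocks, which the protocol neither states nor excludes.
- **Imbalance by chance is not bias.** This stands. The comparison is unbiased on average, and the likely shift is small against the standard error unless hospitals differ a great deal.
- **The standard error errs on the safe side.** If allocation is in effect blocked by site, omitting site makes it too large. That costs power and does not raise the false-positive rate.
- **Adjustment is not ruled out.** The optional clause in section 2.11 could admit institution, so saying that there is no adjustment would go too far. But the clause is discretionary, partly data-driven, and does not name institution.
- **Detail may sit elsewhere.** A full protocol or SAP may describe the division and add the term, and no fault attaches to leaving it there. The point rests on what this article does fix: a randomisation method and a list of model terms that leaves institution out.

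**Conclusion.** The point holds in a limited form. The protocol fixes unstratified blocks, holds envelopes at three hospitals without saying how the list is divided, and states a primary model with no pre-specified adjustment for institution. The consequence is some lost precision or added noise, not bias and not an inflated error rate.

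The gain over the planned power of 0.81 is about 2 to 4 points if site explains 5 to 10% of the variance. It is about 1 to 3 points once the precision already gained by blocking, or the 3% cost of scattered allocation, is counted. It vanishes if site explains little. The variance share and the site sizes are assumptions; the protocol gives neither. The required sample size does not change. The change is worth making because it is cheap and the usual care arm is small and bears on every confirmatory test.

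**What to change.** 1. Pre-specify institution as a fixed effect in the primary and secondary models, separately from the optional covariate clause.
2. State in section 2.6 how the list was divided among the hospitals. If envelopes have been issued, document this and leave the allocation as it is.
3. Only if the list has not been issued, generate one permuted-block list per institution at 2:2:1 and describe randomisation as stratified by institution.

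**Cost.** The model term uses 2 degrees of freedom and, if allocation was scattered and site explains little, inflates the variance by about 3%. Separate lists may leave the totals a few participants away from 56/56/28, because each site can end on an incomplete block. They also make upcoming allocations easier to guess, since blocks of 5 and 10 would be completed within one hospital where the investigator sees each assignment. That is a reason to prefer the model term alone if recruitment has begun.
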